***If no***

Principal reason for premature termination:

☐Patient vomited the study drug a second time and received rescue treatment before PQ was given

☐Early Treatment failure before PQ was given

☐Patient found to be severely G6PD deficient and excluded before PQ treatment was given

☐Patient withdrew consent

☐Lost to follow up

☐Death

☐ Other: please specify………………………………………………

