## Exclusion Criteria

- Bodyweight <6kg
- Presence of general danger signs in children aged under 5 years or signs of severe malaria according to the definitions of WHO (Annex III)
- Presence of severe malnutrition^[[1]](#footnote-1)^
- Acute anaemia <8g/dL
- Regular medication, which may interfere with antimalarial pharmacokinetics
- History of hypersensitivity reactions or contraindications to any of the drug(s) tested or used as alternative treatment(s)
- A positive pregnancy test or lactating.
- Severe G6PD deficient patients will be excluded from PQ treatment

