**Table: Maximum amount of venous blood collected on d0 / body weight**

| **Patient’s approximate weight in kilograms** | **Amount (mL)** |
| --- | --- |
| >6 to 7 | 4-5 |
| >7 | 5 |

All participants will be followed daily until day 2 to provide supervised treatment and ensure clinical and parasitological recovery following chloroquine (Pv arm) or artemether-lumefantrine (Pf arm and Pf/Pv arm) treatment.

Thereafter patients (excluding those with severe G6PD deficiency) will be given unsupervised primaquine for 1 dose (Pf arm) or 14 doses (Pv/mix arm) and reviewed again after 7 days (day 9), 14 days (day 16), 21 days (day 23) and 28 days (day 30). All P. vivax and mixed infections will in addition be followed up after 3 and 10 days (day 6 and 12 respectively) to assure the safety of the provided treatment. Any patient developing signs and symptoms indicative of a malarial episode or an adverse event within the follow up period will be asked to re-attend the clinic for an unscheduled visit, where they will be offered clinical management according to local clinic guidelines. A fingerprick will be performed during every follow up and unscheduled visit, 5ml of blood will be collected for every recurring malaria episode (see table below). Information on adverse events will be collected during every visit. Whenever possible a pill count will be performed on day 16.

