## Rescue treatment

Treatment failure (see Annex VII) are treated according to national guidelines with quinine (Annex VI). This will be noted on the CRF. If the participant has started PQ treatment he will be asked to return for all scheduled follow up visits.

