## Patient withdrawal and protocol violation

- Withdrawal of consent. A patient may withdraw consent at any time, without prejudice for further follow-up or treatment at the study site.
- Protocol violation (e.g. enrolment violation or incomplete treatment). Patients with any protocol violation will be followed up as scheduled for safety assessment. This also includes patients with serious adverse events that necessitate termination of treatment before the full course is completed.

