**End of study assessment**

The patient completed follow up until day 16 ☐ Yes ☐No

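### The protocol contradicts itself on scheduled follow-up for enrolled patients who never start primaquine, and one reading drops severely G6PD deficient patients from the 30-day endpoints

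*Protocol*

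**What the plan says.** Three places suggest that a patient who never starts PQ leaves scheduled follow-up.

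- **Annex IX, End of study assessment.** The form asks whether "The patient completed follow up until day 16". If not, it asks for the principal reason for premature termination. Three of the printed reasons are that PQ was not reached: "Patient vomited the study drug a second time and received rescue treatment before PQ was given", "Early Treatment failure before PQ was given" and "Patient found to be severely G6PD deficient and excluded before PQ treatment was given".
- **Rescue treatment.** The return instruction is conditional: "If the participant has started PQ treatment he will be asked to return for all scheduled follow up visits". Nothing is said about a rescued patient who has not started PQ.
- **Study Procedures.** "Thereafter patients (excluding those with severe G6PD deficiency) will be given unsupervised primaquine for 1 dose (Pf arm" opens a sentence that goes on to set the reviews on days 9, 16, 23 and 30.

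Three places suggest the opposite.

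- **Exclusion Criteria.** "Severe G6PD deficient patients will be excluded from PQ treatment". The exclusion is from the drug, not from the study.
- **Patient withdrawal and protocol violation.** Incomplete treatment is given as an example of a violation, and "Patients with any protocol violation will be followed up as scheduled for safety assessment".
- **Synopsis and Treatment & sample collection.** The Synopsis gives 30 days of follow-up for both species. The treatment section asks all patients in each species group to return up to day 30. Neither makes this depend on PQ.

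**The concern.** Death, loss to follow-up and withdrawal explain why a patient cannot be seen. Not receiving PQ does not, yet the form puts all of them in one list headed by termination. Site staff who work from the form could reasonably stop scheduled visits once PQ is withheld. Staff who work from the Synopsis or the treatment section would continue them.

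The choice changes the data. Recurrence within 30 days (Efficacy endpoints) and late failure (Annex VII) are defined without reference to PQ, and CQ efficacy against vivax is a secondary objective. The Hb, anaemia and adverse event proportions (Safety endpoints) are stated for patients, not for PQ recipients. The denominators of these endpoints therefore depend on which passage is followed. For severe deficiency, the patients removed would be selected by G6PD activity, which is itself a study variable.

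**Working it through.** The sample size has no power or precision calculation, so there is no planned figure to reproduce. The check compares the text, counts visits and bounds the number affected.

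**1. When termination would occur.** The G6PD result is entered on the Day 2 form, and PQ starts on day 3. A G6PD-based termination would therefore fall around day 2-3. Second vomiting can occur at the supervised doses on days 0-2. Early failure is defined on days 1-3 (Annex VII).

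**2. Fixed visits lost (optional day 3 not counted; days from Treatment & sample collection).**
- Vivax and mixed: days 0, 1, 2, 6, 9, 12, 16, 23, 30 = 9 visits. After day 3: 6, 9, 12, 16, 23, 30 = 6.
- Falciparum: days 0, 1, 2, 9, 16, 23, 30 = 7 visits. After day 3: 9, 16, 23, 30 = 4. The schedule table marks day 12 instead of day 9 in the falciparum follow-up row, but the count of 4 is the same.

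**3. Which rule reaches which group.**
- *Second vomiting with rescue.* The course is cut short, which fits incomplete treatment, so the violation rule calls for scheduled follow-up. The CRF lists it as a termination reason. This is a direct conflict.
- *Severe G6PD deficiency.* Withholding PQ is the protocol's own instruction, so the violation rule does not clearly apply. The conflict is between the CRF and one reading of Study Procedures on one side, and the Exclusion Criteria, Synopsis and treatment section on the other.
- *Early failure before PQ.* This is a defined outcome, not a violation. The conditional return clause and the CRF suggest an end to visits. The Synopsis and treatment section do not.

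**4. How many patients.** Inputs: target 50 + 160 = 210 (Sample Size); G6PD deficiency of any degree 20-40% in the local population (Rationale and Aim). The severe share is not stated, so 10-50% of the deficient is assumed.
- Deficient: 0.20 × 210 = 42 to 0.40 × 210 = 84.
- Severe: 42 × 0.10 = 4.2 to 84 × 0.50 = 42, which is 2-20% of 210.
- Vivax: 50 × 0.20 × 0.10 = 1 to 50 × 0.40 × 0.50 = 10.
- Falciparum: 160 × 0.20 × 0.10 = 3.2 to 160 × 0.40 × 0.50 = 32.

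No rates are given for second vomiting or early failure, so those groups cannot be sized.

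**5. Which endpoints are touched.** Severely deficient patients who completed CQ or AL remain evaluable for 30-day recurrence and for the Hb and adverse event proportions, and would lose both. Early failures have already failed, and Annex VII removes them from late failure. After quinine rescue, a later recurrence no longer tests CQ or AL. For these two groups the loss is therefore mainly of Hb and adverse event data.

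**The case against.** The strongest reply is that the CRF does not order anyone to stop. It records a reason only when day-16 follow-up was not completed, and a severely deficient patient who attends to day 16 is recorded as complete. The parenthesis in Study Procedures can be read as limiting only the PQ supply. The schedule table sets visits by species with no exception for patients without PQ. All of this stands. It means that termination is one possible reading, not an established instruction. It does not remove the conflict, because a printed list of termination reasons that includes not being given PQ invites that reading, and the conditional clause under Rescue treatment supports it.

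Several stronger readings are tempting, and the documents do not support them.

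- A reader might infer a plain breach of the violation rule for all three groups. That rule clearly reaches only second vomiting with rescue.
- A reader might see the severely deficient as the highest-risk patients going unobserved. Their particular risk comes from PQ, which is withheld. They are seen on days 0-2, and any patient with symptoms or an adverse event during follow-up is asked to attend an unscheduled visit.
- A reader might call them the only unexposed patients and say that a control group is lost. Patients may also decline at the second consent or not take the unsupervised tablets. The planned relative risk covers only participants treated with 14 days of PQ, so no planned unexposed comparison is lost. The groups without PQ would also make a poor reference, since they mix severe deficiency, vomiting and rescued failures.

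The numerical range is also soft. The 20-40% refers to the local population, while the Background says that deficiency protects against vivax, so the vivax figures may be too high.

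**Conclusion.** The protocol is inconsistent on whether enrolled patients who never start PQ keep their scheduled visits. The conflict is direct for second vomiting with rescue, and an unresolved ambiguity for severe G6PD deficiency and early failure. This conclusion rests on the text alone.

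If the termination reading is followed, each affected patient loses 6 of 9 fixed visits (vivax or mixed) or 4 of 7 (falciparum). The consequence that matters most is selective loss, by G6PD status, of severely deficient patients who completed CQ or AL from the 30-day recurrence endpoint and from the all-patient Hb and adverse event proportions. The range of about 4 to 42 of 210 depends on the assumed 10-50% severe share and on applying the local prevalence to the study population. It indicates scale only.

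**What to change.** - Reconcile the Exclusion Criteria, Study Procedures, Treatment & sample collection, Rescue treatment, Patient withdrawal and protocol violation, and the Annex IX end-of-study form. State in one place whether patients not given PQ keep the study visits already scheduled for their species group (Hb, microscopy and adverse events as set out there) to day 30. Keeping them preserves the endpoints as now defined. If they are not kept, the endpoint denominators should say so.
- In the CRF, use two separate items: *PQ not given: reason* and *follow-up ended: reason* (withdrawal, loss to follow-up, death). Not receiving PQ then does not by itself end data collection.
- Report patients not given PQ separately and descriptively, by reason, and not as a control group.

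The cost is wording in the protocol and CRF, plus 4 to 6 existing visits per affected patient. For severe deficiency, under the assumption above, that is about 1 × 6 + 3.2 × 4 = 19 to 10 × 6 + 32 × 4 = 188 visits in total. No new procedure is needed, and no treatment or rescue rule is proposed.

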# Annex X

Signs and symptoms that justify an unscheduled visit:

- Sudden onset of fever
- Disorientation / dizziness / impaired consciousness
- Severe gastro-intestinal symptoms
- Rash
- Severe and persistent headache
- Signs of severe haemolysis
- Signs of severe methemoglobinemia
- Any other sign of illness that worries the patient enough to seek care

# Annex XI

Timeline

| **Month** | **1** | **2** | **3** | **4** | **5** | **6** | **7** | **8** | **9** | **10** |
| --- | --- | --- | --- | --- | --- | --- | --- | --- | --- | --- |
| **Protocol development** | X |  |  |  |  |  |  |  |  |  |
| **Ethics approval** |  | X |  |  |  |  |  |  |  |  |
| **Site preparation** |  | X | X |  |  |  |  |  |  |  |
| **Patient enrolment** |  |  |  | X | X | X | X | X | X |  |
| **Study closure** |  |  |  |  |  |  |  |  | X |  |
| **Analysis and publication** |  |  |  |  |  |  |  |  | X | X |

1. defined as a child whose growth standard is below –3 z-score, has symmetrical oedema involving at least the feet or has a mid-upper arm circumference < 110 mm) [↑](#footnote-ref-1)
